## Abstract

**Background:**

While the HPV vaccines have been approved by the US FDA since 2006, in recent years an increasing number of women are living with cervical cancer globally. Among them, Chinese women have a higher cervical cancer incidence and mortality rate than the global average, with mortality rates being almost twice the global average. However, the current approach of HPV vaccination in China is not satisfactory given the high disease burden of cervical cancer. The current study is a randomized controlled trial designed to identify the barriers and facilitators of HPV vaccination among Chinese female students. This study will also test a health intervention measure via a popular form of new media in order to improve the HPV vaccine uptake under the framework of Information-Motivation-Behavioral skill Model (IMB).

**Methods:**

This investigation is a multicenter, school-based, prospective, randomized, parallel group, double-blind, blank-controlled trial involving a 7-day education intervention with a further 6-month follow-up. We will enroll at least 3360 participants older than 18 years. The enrolled participants will be randomly divided into two groups (1:1 ratio). The intervention group will be offered a 7-day mobile health education, and participants in both groups will fill out 4 questionnaires at the baseline, 1 month, 3 months and 6 months after the intervention. The primary outcome is the difference in HPV vaccination or reservation for the HPV vaccine between the intervention and control groups. Secondary outcomes will include the comparison of (1) knowledge, attitudes, motivation, beliefs and behavioral skill about HPV and cervical cancer prevention, and (2) the willingness to uptake HPV vaccination.

**Discussion:**

This study will examine the theory-based intervention in improving HPV vaccination among Chinese female college students. We will conduct the randomized controlled trial to provide scientific evidence on the potential effect of the IMB theory-based intervention. Findings from this study will contribute to a growing research field which assesses the effectiveness of mobile-based, school-targeted and theoretically guided interventions for promoting HPV vaccination in adolescents.

**Trial registration:**

Chinese Clinical Trial Registry (ChiCTR), ChiCTR1900025476; Registered on 27 August 2019.

## Background

Globally, cervical cancer is the fourth most common malignant tumor in women, with an incidence of about 6.6% and a mortality rate of 7.5% [1]. In 2018, about 570,000 new cases of cervical cancer were diagnosed and 310,000 deaths were reported [1]. Among these, low and middle-income countries account for 86% of new cases and 88% of deaths worldwide [1]. In China, cervical cancer is more prevalent than the global average, with the cancer being the second most common malignant tumor among Chinese women [2]. In 2018, the age-standardized incidence rate of cervical cancer among Chinese females was still as high as 10.7% [3], although China has introduced HPV2 (Cervarix), HPV4 (Gardasil) and HPV9 (Gardasil) to the mainland between 2016 to 2018 to cope with the burden of cervical cancer caused by HPV-16 and HPV-18 [4].

While the safety and efficacy of the HPV vaccine has been widely recognized by authoritative organizations and institutions, HPV vaccination rates are still low in mainland China [5–10]. Data from the National Cancer Center suggests that a lack of knowledge on HPV and cervical cancer may be a barrier to HPV vaccination [10, 11]. Studies have also found that Chinese adolescents have a low awareness of HPV vaccination [12, 13]. Other barriers to cancer prevention for Chinese women include cultural beliefs on sexuality and widespread vaccine hesitation or rejection due to misconceptions about HPV prevention [14, 15]. In addition, HPV vaccination has not been publicly provided in China. Instead, citizens must pay for the HPV vaccine at their own expense.

Despite the importance of the HPV vaccine for cervical cancer prevention, limited information has been available on how to improve HPV vaccination among Chinese people [16, 17]. Before the HPV vaccine got approved in mainland China, an intervention study conducted in the junior middle schools of Chengdu, China, found an increase in student willingness to be vaccinated from 56.5 to 88.4% (*p* < 0.001) after 1-h of health education [16]. Similar to the school-based study, the HPV vaccine acceptability has also been observed to increase among employed women and female undergraduate students after an informative group lecture [17]. However, the results of the above mentioned studies did not include the HPV vaccination rate as one of the assessment indices of the intervention. Thus, there is an urgent need to develop effective intervention strategies to improve HPV vaccination among Chinese women, especially using the HPV vaccine uptake as the primary outcome.

Results from the successful promotion experiences of the HPV vaccine abroad suggest that employing culturally tailored and theory-based education could positively influence participants to receive the HPV vaccine, especially if school-based intervention is targeted at adolescent females [18, 19]. Perhaps this is due to a combination of cultural ideals valuing school as a place for students to gain new knowledge, the emerging sexual needs of students and the higher HPV infection rate among adolescents [20–22]. In addition, given the widespread usage of mobile phones among young adults and the ability of mobile phone technology to overcome location and time restrictions, a mobile-based health intervention could be a low-cost and effective method to reach populations with low HPV vaccination rates [23, 24].

Given the emerging need for increased HPV vaccination among Chinese women in recent years, the current study will test the effects of a mobile-based intervention on Chinese female college students (see Fig. 1 for conceptual framework), guided by the Information- Motivation- Behavior skill model (IMB) [25]. Specifically designed for the HPV vaccine uptake study, the IMB model constructs used in this study include information relating to HPV and the HPV vaccine for cervical cancer prevention, HPV vaccination motivation, and some useful behavioral skills to ensure HPV vaccination [26].

**Fig. 1 Fig1:**
[figure not shown]
Conceptual Framework of the Study

**Fig. 2 Fig2:**
[figure not shown]
Flow diagram of the study

We hypothesize that a mobile-based approach combining theory-based education and information about HPV, cervical cancer and the HPV vaccine may significantly improve HPV vaccination rates among participants.

Therefore, the primary objective of this study is to investigate the efficacy of a 7-day mobile-based intervention designed to increase HPV vaccination among Chinese female college students. The secondary objectives are to: (1) explore the impact of the intervention on knowledge, attitudes, and beliefs about HPV, cervical cancer and the HPV vaccine, (2) evaluate the short-term effect on uptake intention of the HPV vaccine, (3) determine the factors associated with the willingness of vaccination uptake and (4) identify the factors influencing HPV vaccination.

## Methods/design

### Trial design

This is a multicenter, school-based, prospective, randomized, parallel group, double-blind, blank controlled trial involving a 7-day education intervention with a further 6 months follow-up. A total of 3360 individuals over 18 years old will be randomized to: (1) intervention group: this group will receive a baseline questionnaire followed by a 7-day mobile health education, and 3 questionnaire surveys at 1 month, 3 months, and 6 months after the intervention, or (2) control group: this group will receive 4 questionnaire surveys conducted simultaneously with the intervention group. This study protocol is reported in accordance with the Standard Protocol Items: Recommendations for Interventional Trials statement, and results will be reported in line with the Consolidated Standards of Reporting Trials (CONSORT) statement and the CONSORT statement for non-pharmacological interventions [27–29].

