### Recruitment and informed consent

All enrolled participants will be informed of the research objectives, the study procedures, their rights and obligations, the expected benefits and the possible risks to the participants before they sign the informed consents (Appendix). Participants in the study will also have the right to freely obtain more information at any time and will be allowed to freely withdraw from the study without restrictions at any research stage.

Once each participant signs the informed consent, the researchers will complete the eligibility checklists and records will be made of any candidate who fails to meet the inclusion criteria. Additionally, in order to facilitate follow-up services, we need participants to leave a mobile phone number or WeChat account. All of the above information is stored on an encrypted laptop and kept by a dedicated person with strict information confidentiality.

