### Sampling and randomization

The study process consists of the following four phases:

Phase 1: Confirm the stratified sampling framework by geographical territories of China.

The stratified sampling of the 31 provinces/municipalities/autonomous regions in China is conducted from seven geographical territories, namely East China, South China, Central China, North China, Northwest China, Southwest China and Northeast China.

Phase 2: Convenient sampling to determine the cities and universities to be included within the geographic territories in Phase 1.

We select a representative city in each of the seven geographical territories using the convenient sampling method. A total of 7 cities (Jinan of Shandong Province, Guangzhou of Guangdong Province, Zhengzhou of Henan Province, Beijing, Urumqi of Xinjiang Uygur Autonomous Region, Chengdu of Sichuan Province, Dalian of Liaoning Province) were finally decided to be the study sites. In each representative city, a comprehensive university is selected. A total of 7 universities (Shandong University, Zhongshan University, Zhengzhou University, Capital Normal University, Xinjiang University, Sichuan University, Dalian University of Technology) are finally confirmed as research centers for this study.

Phase 3: Cluster sampling in each of the seven research centers.

After satisfying the inclusion criteria, at least 240 university students will be selected by class from the literature and science majors (excluding medical majors) respectively, and a total of 480 samples will be composed at each of the seven centers. This selection will result in a total of at least 3360 participants across 7 schools.

Phase 4: Randomization and allocation in each center.

After the baseline survey, all identified participants will be randomly assigned to the intervention group or control group in a 1:1 ratio, and each group at each center will have 240 participants. Randomization will be stratified with regards to majors, resulting in two separate categories of literature and science majors. The random sequence will be generated using SAS V.12. (SAS Institute) software. Furthermore, randomization will be conducted by personnel not involved in the trial at each of the seven universities.

After randomization, the researcher who assigns participants to the intervention will provide information about the mobile-based education. This researcher will no longer be blinded from this point.

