### Blinding

In this investigation, all researchers involved in outcome assessments will be blinded to the group allocation of participants. During the intervention period, only unblinded researchers will be in contact with participants enrolled in the trial. In addition, all data analysis will be completed by personnel who are blinded to the intervention assignment. Participants will be unblinded after the 6 months and 7 days of assessment.

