The mobile health intervention contains a high level of interactivity. Participants will be allowed to engage in mutual conversation amongst themselves on different topics of intervention. Based on the mobile application, the intervention group and the control group at each center will establish a chat group respectively, and the administrator will automatically upload 10 min of educational content in the intervention chat group only. After completing the learning session, participants can perform punching and talk about the educational content.

Control group(no intervention/ black control).

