#### Intervention procedure

Upon completion of the baseline assessment, two research staff will anonymize and number the students. The staff will then randomize participants to either the intervention group or control group. The intervention and control group will have at least 240 participants respectively at each of the seven centers. Timing randomization in this way ensures we can balance intervention and control groups on baseline characteristics. One unblinded research staff will remain in contact with participants via the mobile app. The intervention group will receive digital education materials every day during the 7-day intervention period, while the control group will not have any form of intervention. Possible intervention non-attendance and trial non-compliance will be collected and followed up via telephone by the unblinded researcher.

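### The trial is labelled double-blind, but participants can see what they receive and report the vaccination outcome themselves; two sections also disagree on who randomises

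*Protocol article*

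**What the plan says.** **Label.** The Trial design section reads "This is a multicenter, school-based, prospective, randomized, parallel group, double-blind, blank controlled trial involving a 7-day education intervention", and the Abstract uses the same label.

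**Who is blinded.** The Blinding section states that "all researchers involved in outcome assessments will be blinded to the group allocation of participants" and that the data analysts are blinded too. It describes no means of blinding participants, yet says "Participants will be unblinded after the 6 months and 7 days of assessment".

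**What each arm sees.** Under Interventions, each arm at each centre has its own chat group, and "the administrator will automatically upload 10 min of educational content in the intervention chat group only". Under Intervention procedure, the intervention arm receives material daily for seven days, "while the control group will not have any form of intervention". Under Recruitment and informed consent, "All enrolled participants will be informed of the research objectives, the study procedures", before they sign.

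**Where the outcome comes from.** Outcome measures includes receipt of, or an appointment for, a first HPV vaccine dose. Measures and Statistical analysis say the data come from electronic questionnaires that participants complete and upload.

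**Who randomises.** Sampling and randomization (Phase 4) says "randomization will be conducted by personnel not involved in the trial at each of the seven universities". Intervention procedure says two research staff anonymise and number the students, and then: "The staff will then randomize participants to either the intervention group or control group". Phase 4 also mentions a researcher who assigns participants to the intervention and is unblinded from that point.

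**The concern.** A double-blind label tells the reader that neither participants nor those measuring the outcome know the allocation. Here a participant in the education arm cannot be unaware of seven daily lessons. She is also the person who states whether she has been vaccinated or has booked. Women who have just been taught why vaccination matters may be more inclined to report a dose or a booking than women taught nothing. A booking is the softer of the two events. A difference in reporting of this kind would appear as a treatment effect, and the large pooled sample can make a small one significant.

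The conflict over who randomises is a separate matter. A reader needs to know whether the people who number the students are independent of those who allocate them, and the article gives two answers.

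**Working it through.** **1. Can participants be blind?** Setting the sections side by side:

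- *Intervention arm.* Daily HPV content, logging of completed sessions and discussion in the chat group (Interventions), telephone follow-up of non-attendance (Intervention procedure) and a satisfaction rating asked only of this arm (1-month follow-up). These women know what they receive.
- *Control arm.* No intervention, but the same information on objectives and procedures before consent. Students are sampled by class and then individually randomised (Phases 3 and 4), so classmates may be in different arms. Controls can probably infer their arm. This is likely rather than certain, because the consent text is not available here.
- *Blinding section.* Unblinding participants at 6 months and 7 days presupposes a blind that no section provides.

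**2. What does assessor blinding add?** For vaccination or booking, the participant supplies the answer and it uploads automatically. A blinded researcher has little left to judge. Blinded analysis is still useful, although the satisfaction items could reveal allocation if they sit in the analysis file.

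**3. How much could self-report matter?** The article gives no false-report rate, so the rates below are assumptions shown as a range.

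Inputs:
- 240 per group at each of 7 centres (Sample size calculation): 240 × 7 = 1,680 per arm.
- 20% loss to follow-up (same section): 1,680 × 0.80 = 1,344 per arm.
- Control rate 10% (same section), taken here as the true rate in both arms, so there is no real effect.
- Two-sided α = 0.05.
- *f* = share of intervention women without an event who wrongly report one (assumed). Controls: none (assumed).

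Formulas:
- Reported rate: p₁ = 0.10 + 0.90 × *f*; p₀ = 0.10.
- SE = √{[p₁(1 − p₁) + p₀(1 − p₀)] / 1,344}; z = (p₁ − p₀) / SE.
- Chance of a significant apparent benefit ≈ Φ(z − 1.96).

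| *f* | p₁ | p₁ − p₀ | SE | z | Chance significant | Apparent OR |
|---|---|---|---|---|---|---|
| 1% | 0.109 | 0.009 | 0.0118 | 0.76 | about 12% | 1.10 |
| 2% | 0.118 | 0.018 | 0.0120 | 1.50 | about 32% | 1.20 |
| 3% | 0.127 | 0.027 | 0.0122 | 2.21 | about 60% | 1.31 |
| 5% | 0.145 | 0.045 | 0.0126 | 3.57 | about 95% | 1.53 |

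Example for *f* = 3%: 0.10 + 0.90 × 0.03 = 0.127; SE = √[(0.1109 + 0.0900) / 1,344] = 0.0122; z = 0.027 / 0.0122 = 2.21.

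**4. Sensitivity to over-reporting by controls.** If controls without an event wrongly report one at rate *g*, the spurious difference becomes 0.90 × (*f* − *g*). With *f* = 3% and *g* = 1%, the rates are 0.127 and 0.109, SE = 0.0124, z = 0.018 / 0.0124 = 1.45, and the chance falls from about 60% to about 30%. With *g* = *f* the test keeps its 5% level. Only differential misreporting produces the effect.

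**5. Who randomises?** Phase 4 says personnel not involved in the trial; Intervention procedure says the two research staff who number the students. Both sections place allocation after baseline, and Phase 4 has the sequence generated by software and stratified by major. The conflict concerns who applies the sequence.

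**The case against.** The strongest case on the other side has four parts.

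- **Real protections remain.** Allocation is random and follows the baseline survey, a software-generated sequence is stated, and the analysts are blinded. This stands. A reader might infer that the trial has no protection against bias at all; the article does not support that.
- **The randomisation conflict may be loose wording.** The research staff may simply apply the generated sequence, or may be the outside personnel described differently. Eligibility, consent and baseline all come before allocation. This stands too. A reader might infer that staff can steer assignment, but the text only leaves independence and concealment unclear.
- **Knowledge of allocation is less certain for controls.** The article does not say what is posted in the control chat group, only that educational content goes to the other one. It should not be called empty, and controls' knowledge of their arm is a probable inference.
- **Self-report is an accepted limitation in a behavioural trial, and the illustration rests on assumed rates.** Correct. The article may also omit verification detail that the full protocol holds. Knowledge items, also listed under Outcome measures, are less open to this bias than a claimed dose or booking. The point nevertheless does not depend on an omitted detail. The stated label and the unblinding sentence conflict with the stated design, and the Discussion's limitations mention neither self-report nor the lack of participant blinding.

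**Conclusion.** The point holds in a limited form. The double-blind label and the sentence on unblinding participants are inconsistent with the design as described. For self-reported vaccination or booking, blinding the outcome researchers adds little, but it would be wrong to say it protects nothing across all outcomes. The two accounts of who randomises must be reconciled; they do not show that concealment is lost.

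On size, a false-report share of 1% to 5% confined to the intervention arm would raise the chance of a significant result, with no true effect, from 5% to between about 12% and 95%. This assumes 10% true uptake in both arms, 1,344 analysed per arm and no over-reporting by controls. The shares are not in the article, and the figures shrink as controls over-report. They show how sensitive the result is; they do not predict that a bias of this size will occur. An open design is defensible for an education trial, and the corrections are worth making because they are cheap.

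**What to change.** 1. In the Abstract and Trial design, replace the double-blind label with: open-label for participants, with blinded outcome researchers and data analysts. Delete the participant-unblinding sentence from Blinding.
2. Reconcile Phase 4 with Intervention procedure, so that the independent personnel allocate from the pre-generated sequence to a locked list of study numbers. The two research staff would then only anonymise and number the students.
3. Add one upload item to the existing questionnaires for women who report a dose or a booking (photo or screenshot of the vaccination or booking record). Pre-specify a supportive analysis that counts documented events only.
4. Add self-report without participant blinding to the limitations in the Discussion.

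Items 1, 2 and 4 change wording only. Item 3 costs one extra field for the women who report an event. Its drawback is that some genuine events will lack a document, so the analysis should be supportive and should not replace the primary one.

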### Study setting

To ensure the representativeness of the research findings, we will recruit participants from seven comprehensive universities located in seven geographical territories of China: Shandong University in East China, Zhongshan University in South China, Zhengzhou University in Central China, Capital Normal University in North China, Sichuan University in Southwest China, Dalian University of Technology in Northeast China, and Xinjiang University in Northwest China. The reasons for selecting these colleges is that they are located in cities with relatively advanced political and economic levels in their respective geographical territories and are all top-ranking comprehensive universities. Thus, the research settings can ensure the balance of background features to a large extent. All researchers and support staff in this project will be trained based on the same training protocols and are required to have an educational background in public health. This study follows the regulations of *Measures for the Ethical Review of Biomedical Research Involving Humans (*Implemented on December 1, 2016) of the National Health Commission of the People’s Republic of China. All participants will sign an informed consent after they agree to attend the study and before the baseline survey. This study is planned to be carried out in November 2019 and last for about 7 months.

